### Handling missing data

Missing data will be handled using multiple imputation, which will ensure that as minimal as possible incomplete data are dropped. We will create numerous data sets containing different estimates of the missing values maintaining key identifying variables such as age, gender, testing frequency and distribution location, as well as distribution model. Imputed data will be pooled into a study data set for analysis.

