## Methods and analysis

### Study design

The study is a secondary analysis of routinely collected programme data from a prospective study aims at evaluating different HIVST distribution models implemented during November 2017 and December 2020 by Ezintsha, a subdivision of Wits RHI (see Data collection section). The different models implemented by Wits RHI are based on the NDOH HIV Self Screening Guidelines and are presented in table 1. Briefly, the models included community-based, public sector facility, key population and private sector targeted distribution. Each model had different channels and implementation strategies.

**Table 1 T1:** HIV self-testing distribution models implemented by Wits RHI/Ezintsha

Model	Modality	Description
Community-based distribution	Hotspots	HIVST was offered to high-risk populations at hotspots through fixed pop-up sites. Hotspots include high foot traffic areas such as busy walkways or shopping centres. After a peer educator provided a demonstration on how to use HIVST kits, clients were provided with a choice to take a kit home or to use it onsite either on their own or with the assistance of the distributor. Clients opting to test onsite were given an opportunity to confirm reactive results. All women and men who indicated having a male partner were offered an HIVST test kit for their partners. 5% of consenting primary recipients of HIVST were telephonically followed up for outcomes of HIVST use, result, linkage to care and uptake of ART. From November 2019, all consenting clients were offered a choice to self-report their outcomes using one of the three mhealth platforms, specifically, WebApp, WhatsApp or on the interactive voice response system.
	Transport hub	The description of this modality is the same as the community-based hotspot modality, with a specific focus on distribution in transport hubs, including taxi ranks and train stations.

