### Statistical analysis

Data for the secondary analysis will be deidentified and the analysis will be conducted between April and July 2021. Continuous variables will be expressed as means (±SD) or median and IQR as appropriate. Frequencies and proportions will be used to describe categorical variables. Binomial test will be used to determine whether the proportion of linkage to care and receipt of treatment among HIVST users equal to a prespecified proportion based on a recently published South Africa HIVST study.^17^ Differences in the proportions of linkage to care and receipt of treatment among HIVST users by distribution modality and other sociodemographic characteristics will be assessed using χ^2^ test or Fisher’s exact test, as appropriate. Unadjusted and multivariable adjusted relative risks of linkage to care and receipt of treatment among HIVST will be calculated using modified Poisson regression with robust variance estimation. Risk ratios and 95% CIs for the risk ratios will be reported. A two-tailed p value of <0.05 will be considered statistically significant. All analyses will be performed using STATA and SAS V.9.4.

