### Limitations

Our analysis plan could have limitations as follows. First, limited generalisability of the findings, given participation in self-reporting, is voluntary and not randomised. We recognise a high proportion of self-reporting a strong determinant of generalisability of the findings; therefore, we aimed to follow up as far as possible all consenting clients with as many as three reminders/engagement opportunities presented via the different self-reporting platforms. Second, we are prone to validity and reliability of secondary data, particularly where data are incomplete. The project monitoring and evaluation team aims to ensure the completeness of data. In addition, analysis will be conducted on pooled imputed data sets to ensure that as minimal as possible incomplete data are dropped. Third, we acknowledge that both obtaining and reporting HIV test results are open to social desirability and non-response biases. The project provided self-reporting options to HIVST recipients and ensured anonymous reporting of HIVST use and results data. Fourth, while the analyses will provide results on the outcome for the different distribution modalities, the larger focus of the project and results are to provide preliminary evidence to create a supportive environment for the introduction and integration of HIVST in national policies, strategies, plans and regulations at the country level. Thus, the focus is less about comparison between different distribution modalities and more about piloting different implementation strategies to collect preliminary data to inform national policies, selection, adaptation, and scaling up of different HIVST delivery and linkage models for different populations.

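### The article pools the imputed data into one data set before analysis; followed literally, this drops the between-imputation variance and makes CIs too narrow and p values too small

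*Protocol article*

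**What the plan says.** The Protocol article, Handling missing data, opens with the aim: "Missing data will be handled using multiple imputation, which will ensure that as minimal as possible incomplete data are dropped". It continues "We will create numerous data sets containing different estimates of the missing values" and ends "Imputed data will be pooled into a study data set for analysis". The thing pooled is data, the destination is a single data set, and analysis comes afterwards.

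The Limitations section returns to the subject: "analysis will be conducted on pooled imputed data sets to ensure that as minimal as possible incomplete data are dropped". This echoes the order, though in the plural and in less technical language.

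The Statistical analysis section lists a binomial test against a prespecified proportion, χ² or Fisher's exact tests across modalities and sociodemographic groups, and relative risks "calculated using modified Poisson regression with robust variance estimation". On reporting it says "Risk ratios and 95% CIs for the risk ratios will be reported" and "A two-tailed p value of <0.05 will be considered statistically significant". No section describes a step in which estimates or variances from several imputed data sets are combined.

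**The concern.** Several imputations are made so that their spread can measure the uncertainty due to the missing values. That spread enters the standard error only if each completed data set is analysed separately and the results are then combined. Merging the data first leaves nothing from which to estimate it.

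The robust variance in the Poisson model does not make up for this. It corrects for using a Poisson working variance with a binary outcome; it does not know which values were imputed, nor that several rows may belong to one person.

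Risk ratios with 95% CIs and tests at 0.05 are the article's inferential output. The Limitations section plays down comparison between modalities, but the Discussion expects the findings to show which channels work best and merit adoption in national policy. Differences that pass 0.05 only because the standard error is too small could feed into that.

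**Working it through.** **Inputs.** The article gives α = 0.05 two-sided, 95% CIs, and modified Poisson regression with robust variance. It gives no M, no missing fraction, no rule for turning several data sets into one, and no sample size, so there is no stated figure to reproduce. Assumed ranges: M = 5 to 20; 10%, 30% and 60% of outcomes missing.

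**Notation.** W is the average within-imputation variance and B the between-imputation variance. Rubin's total variance is T = W + (1 + 1/M)B, and the fraction of missing information is L = (1 + 1/M)B/T, so W = (1 − L)T. If r is the reported SE divided by the estimate's true SE, then type I error = 2[1 − Φ(1.96r)] and coverage = 2Φ(1.96r) − 1.

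**Reading 1: M copies stacked, rows treated as independent.** The reported variance is about W/M, so r = √((1 − L)/M).
- L = 0, M = 5: r = √(1/5) = 0.447; type I error 38%.
- L = 0, M = 20: r = √(1/20) = 0.224; type I error 66%.

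This inflation comes from counting each person M times and arises even with almost nothing missing.

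**Reading 2: one completed data set treated as real.** The reported variance is W. A single random completion also adds its own noise, so for large M the estimate's true variance is T + B = T(1 + L), and r = √((1 − L)/(1 + L)).
- L = 0.1: r = √(0.9/1.1) = 0.905; type I error 7.6%.
- L = 0.3: r = √(0.7/1.3) = 0.734; type I error 15%, coverage 85%.
- L = 0.5: r = √(0.5/1.5) = 0.577; coverage 74%.
- L = 0.6: r = √(0.4/1.6) = 0.5; type I error 33%.

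**Reading 3: M copies stacked with weight 1/M.** The reported variance is W for an estimate with variance T, so r = √(1 − L). Type I error is 6.3%, 10.1% and 21.5% at L = 0.1, 0.3 and 0.6.

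**Reading 4: imputations averaged to one value per person.** The between-imputation spread is again lost, and imputed binary outcomes become fractions, which the binomial, χ² and Fisher tests cannot take.

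**Simulation check.** Two groups, true risk ratio 1, risk 0.5, n = 400 and 2000, outcomes missing completely at random, proper imputation, 2000 runs per cell. The log risk ratio used the delta-method variance, which equals the robust variance of modified Poisson regression with one binary covariate. Type I error:

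| Outcomes missing | Stacked, M=5 | Stacked, M=20 | One completed set | Stacked, weight 1/M | Rubin's rules |
|---|---|---|---|---|---|
| 10% | 42% | 68% | 7-8% | 6-7% | 4.4-5.2% |
| 30% | 49-50% | 71-72% | 16% | 10-11% | 4.2-5.6% |
| 60% | 59-61% | 76-78% | 31-35% | 22-25% | 5.0-5.5% |

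Formulas and simulation agree closely. With imputed values in use, each literal reading errs in the same direction, and Rubin's rules bring the error back to about 5%.

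**The case against.** The strongest reply is that the sentence is shorthand. Stata and SAS, both named in the article, normally keep all imputations in one file indexed by imputation number, and the standard commands then analyse each and combine the results. The wording could describe that file. The Limitations sentence, being plural, also fits ordinary multiple imputation and is only weak corroboration. This stands as a possibility. It does not remove the point: the article is not silent on the step but describes one, and nothing in it tells the analyst to combine estimates rather than data.

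A reader might infer that every interval in the study will be far too narrow. The documents do not support that. The extreme figures need unweighted stacking. With one completed set or 1/M weights and about 10% missing, the type I error is 6-8%. If one record per person is kept, analyses that use no imputed values are unaffected.

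A reader might also infer heavy missingness from the follow-up design, since for the hotspot modality "5% of consenting primary recipients of HIVST were telephonically followed up for outcomes of HIVST use, result, linkage to care and uptake of ART". That figure cannot be turned into a missing fraction. The outcomes concern users who report a reactive result, the result and linkage questions belong to one questionnaire, mHealth reporting was added later, and the article does not say whether non-responders are imputed.

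Finally, a reader might infer that the imputation model omits the outcomes. The listed variables are given as examples, so that is not shown.

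**Conclusion.** The point holds in a conditional form. As written, the order of pooling and analysis is reversed. An analyst who followed the text would report CIs that are too narrow and p values that are too small wherever imputed values enter. The direction is certain on the literal readings, but the size is not: it runs from slight (6-8% instead of 5%, at about 10% missing, without unweighted stacking) to extreme (38-66% from stacking alone).

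These sizes rest on assumed M and missing fractions and, in the simulation, on outcomes missing completely at random in a simple two-group comparison. If the authors meant standard pooling of results, only the wording is at fault, but it still needs correcting because it describes a different procedure.

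**What to change.** In Handling missing data, replace the last sentence with: *Each imputed data set will be analysed separately, and log risk ratios and their robust variances will be combined by Rubin's rules.* Change the Limitations sentence to match.

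Where the binomial, χ² or Fisher tests would use imputed data, name a compatible pooled procedure, for example pooled Wald tests or combined χ² statistics; exact tests do not combine directly.

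The cost is small. It is a change of wording, and the software already named supports it (mi estimate in Stata, PROC MIANALYZE in SAS). The downside is wider intervals than the literal procedure would give, and slightly more analysis work.

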### Patient and public involvement

This study will not involve patients as it is a secondary analysis of routine programme data. HIVST recipients will not be involved in the development of research questions this study. However, findings from preference, usability and acceptability studies from STAR phase II will inform design of distribution approaches in the future. Wits RHI’s community advisory commitees on adolescents, treatments, and prevention together with local community advisory boards provided ongoing guidance towards appropriate processes and procedures for implementation HIVST distribution and follow-up, particularly among adolescents and men for community-based distribution models. We plan to share the findings from this study through reports and presentations at local and international conferences. In addition, we will submit articles for publication to peer reviewed journals for wider visibility and use of the findings.

### Beneficiaries and target audiences

The study findings will contribute to the existing and growing body of evidence on the acceptability and efficacy of deploying HIVST and digital self-reporting and linkage to care platforms to reduce mortality and morbidity from HIV among men, key populations and adolescent boys and girls in South Africa. The project is of interest to a range of audiences, including academic and non-academic practitioners, community gate keepers for public health programmes targeting men and young people, HIV programme implementers, governments and public health funding organisations. A description of the primary and secondary outcomes of this study will help to identify distribution models for government and other funders to invest in scaling up of effective HIVST models. In addition, potential gaps in the implementation approaches and generalised lessons learnt can be drawn and inferred in future HIV programming for similar settings and target populations.

### Limitations

Our analysis plan could have limitations as follows. First, limited generalisability of the findings, given participation in self-reporting, is voluntary and not randomised. We recognise a high proportion of self-reporting a strong determinant of generalisability of the findings; therefore, we aimed to follow up as far as possible all consenting clients with as many as three reminders/engagement opportunities presented via the different self-reporting platforms. Second, we are prone to validity and reliability of secondary data, particularly where data are incomplete. The project monitoring and evaluation team aims to ensure the completeness of data. In addition, analysis will be conducted on pooled imputed data sets to ensure that as minimal as possible incomplete data are dropped. Third, we acknowledge that both obtaining and reporting HIV test results are open to social desirability and non-response biases. The project provided self-reporting options to HIVST recipients and ensured anonymous reporting of HIVST use and results data. Fourth, while the analyses will provide results on the outcome for the different distribution modalities, the larger focus of the project and results are to provide preliminary evidence to create a supportive environment for the introduction and integration of HIVST in national policies, strategies, plans and regulations at the country level. Thus, the focus is less about comparison between different distribution modalities and more about piloting different implementation strategies to collect preliminary data to inform national policies, selection, adaptation, and scaling up of different HIVST delivery and linkage models for different populations.

## Discussion

HIVST has been recommended by the WHO and several studies have demonstrated the its acceptability, feasibility and effectiveness.^2 6^ However, there is limited evidence from implementation science research to provide guidance on how to scale up HIVST in LMICs for different hard to reach groups. The STAR Initiative aims to fill this gap, and the proposed secondary data will be a crucial step in generating the evidence needed to determine preliminary public health outcomes of HIVST in South Africa.^11^ In addition, given the restrictions that COVID-19 has caused on HTS due to lockdown and social distancing requirements,^5 18^ the findings of this study are crucial to inform the implementation and expansion of HIVST in order to sustain HIV testing in a safe and socially distant manner that can help reduce exposure to SARS-CoV-2. The different platforms for HIVST delivery evaluated in this study support the call for scaling up of HIVST during COVID-19 using a variety of strategies to ensure safe and appropriate delivery of HIVST and ongoing HTS.^7^ Beyond the aforementioned implications, the findings will identify which distribution channels work best and should be adopted by the NDOH and included in the national HIVST policy as well as be incorporated in future WHO HIVST implementation guidelines to support national HIVST implementation plans.^16^

The Wits RHI STAR programme was implemented according to South Africa’s national HIV self-screening guidelines. All clients voluntarily received the HIVST kits and consented to follow-up prior to the individuals' participation in the self-reporting surveys. Refusal of HIVST offer or consent to follow-up did not result in loss of access to any existing HTS. The follow-up surveys and secondary data analysis were approved by the University of Witwatersrand Human Research Ethics Committee (ethics reference number 180405). The design and evaluation of the self-report platforms were approved by the University of Witwatersrand Human Research Ethics Committee ethics reference number 171113, and 180 708 for the IVR system, PWA and WhatsApp for business, respectively.

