	Door-to-door	Within a specific mapped community or geographical location, peer educators and/or trained counsellors move from one household to another and offer HIVST to eligible clients residing there. Clients were offered HIVST with the option of either being directly assisted (in the presence of a healthcare provider) or unassisted. Clients who self-report reactive results were offered the option to confirm their results onsite. All women and men who had male partners were offered oral HIVST tests for their partners. To collect information on outcomes of HIVST use, result, linkage to care and uptake of ART, peer educators went back to the residences of all consenting clients.
	Integrated HTS (mobile)	This modality involved the integration of HIVST into existing mobile HIV testing activities. Clients were offered a choice between HIVST onsite or RDT with a counsellor. HIVST kits were distributed to individual clients after a demonstration of how to use them. Clients who opted for HIVST were only offered onsite testing with the option to confirm a reactive HIVST result immediately. Clients who confirmed reactive were referred to nearby health facilities for ART initiation. To collect information on outcomes of linkage to care and uptake of ART, linkage officers checked ART registers of referral health facilities. Integration of HIVST into mobile HTS did not displace traditional blood-based RDT uptake but provided a screening option of increased yield and efficiency for triaging clients for further managed healthcare.
Key population distribution	Sex worker	This modality was implemented alongside the Wits RHI sex worker programme, which provides various health services to sex workers at static sex worker clinics and at outreach sites. Sex workers were offered up to five HIVST kits to take for their network, which would either be their non-client sexual partners, their clients, other sex workers not accessing HTS or a member of the family or friend considered by the sex worker to be at high risk of HIV. This modality was intended to be a secondary only distribution modality; however, sex workers could use one kit for themselves if they needed to test themselves together with one of their recipients. All consenting sex workers were telephonically followed up to determine the usage, linkage to care and ART initiation status of their networks.

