Public sector facility distribution	Outpatient department	Within the hospital outpatient waiting areas, peer educators created awareness and provided information on both traditional RDT and HIVST. Clients were then offered the choice between testing themselves onsite using either a blood or oral-based HIVST test inside a provided cubicle or having RDT with a counsellor. HIVST reactive clients were provided with the opportunity to confirm their results and to be initiated on ART immediately. Offering HIVST alongside traditional rapid testing in the outpatient departments provides clients with not only a choice but also a triage system whereby testers who screen non-reactive using HIVST may exit, allowing counsellors and nurses offering rapid testing enough time to focus on likely reactive testers.
Private sector facility distribution	GP practice and nurse-led clinics	Clients attending health services at GP practices or nurse-led Unjani clinics were offered HIV testing using HIVST during their consultation. After a demonstration was provided by the consulting clinician, clients were offered a private testing space within the facility to test themselves and were asked to self-report their result. Confirmatory testing and ART initiation were available onsite. All clients who self-report a reactive result were offered an HIVST test to take home for their partners.
Private sector distribution	Pharmacy	Pharmacists and pharmacist assistants at private pharmacies offered HIVST to adult clients, 17 and older seeking services that might suggest HIV risk, including emergency contraceptive, treatment for sexually transmitted infections, condoms, lubricants, sexual performance enhancers, etc. After a demonstration is offered, clients can choose to either test onsite on their own or take the kit home. Clients who chose to test onsite were given an opportunity to self-report their result to the pharmacist or the pharmacist assistant. All who self-report a reactive result were offered onsite confirmatory testing when available. All women and men who have male partners were offered oral HIVST tests for their partners. Clients were offered mHealth platforms to self-report on use, result and linkage to care.

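### The Discussion promises to identify the best distribution channels, but Limitations plays down comparison and linkage is ascertained differently across groups of channels, so differences between groups are partly confounded with measurement

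*Protocol article*

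**What the plan says.** Three sections of the protocol article bear on what the study can conclude about channels.

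- **Discussion:** "the findings will identify which distribution channels work best and should be adopted by the NDOH". The same sentence extends the use to WHO implementation guidelines.
- **Limitations:** "while the analyses will provide results on the outcome for the different distribution modalities", the evidence is preliminary and "the focus is less about comparison between different distribution modalities and more about piloting different implementation strategies to collect preliminary data".
- **Statistical analysis:** "Differences in the proportions of linkage to care and receipt of treatment among HIVST users by distribution modality and other sociodemographic characteristics" are to be assessed by χ² or Fisher's exact test, with two-sided p<0.05 as the threshold.

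Table 1 (Study design) describes follow-up modality by modality. For integrated mobile testing, "linkage officers checked ART registers of referral health facilities". For the sex worker modality, "All consenting sex workers were telephonically followed up to determine the usage, linkage to care and ART initiation status of their networks". For GP practices and nurse-led clinics it says "Confirmatory testing and ART initiation were available onsite" but gives no follow-up source. Data collection adds that one set of questions was used on the four self-report platforms: telephone, interactive voice response, WebApp and WhatsApp.

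**The concern.** The Discussion sentence is an unqualified promise to rank channels for national policy. Limitations sets a more modest aim. The analysis in between will produce p values for differences by modality, and these are what a reader would use to support the ranking.

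Those p values compare linkage proportions that were not collected in the same way. An ART register check, a home visit by a peer educator, a woman's account of her partner and a user's own WhatsApp reply can each miss true linkage or record false linkage at a different rate. Between groups of channels the source is largely fixed by the modality, so covariate adjustment cannot fully separate the two. Limitations acknowledges social desirability and non-response in general terms, but not that ascertainment varies by channel. At stake is a recommendation to a health department that may rest partly on how linkage was recorded.

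**Working it through.** **Step 1: outcome source by modality, read from Table 1.**

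| Source of linkage information | Modalities |
|---|---|
| Telephone self-report in a 5% sample, mHealth added in 2019 | Hotspots, transport hub (mHealth from November 2019); workplace (from August 2019) |
| mHealth self-report | Pharmacy |
| Home revisit of all consenting clients | Door-to-door |
| ART registers of referral facilities | Integrated HTS (mobile) |
| Report by the kit recipient about partners or network | Sex worker, antenatal, index testing |
| None stated (services on site) | Outpatient department, GP and nurse-led clinics |

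The 11 modalities fall into six groups. Sources are shared within groups, and in some modalities more than one method was used (telephone and mHealth; telephone or next visit for antenatal). Between groups, source and modality largely coincide. The standard questionnaire covers the four self-report platforms. Register checks and home visits are not among these, and a common question does not make a report about another person equivalent to a user's own answer.

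**Step 2: is there a figure in the plan to reproduce?** No. The article gives no linkage proportion, no number of reactive users by modality and no error rate for any source. What follows is an illustration under assumptions.

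**Step 3: two channels with the same true linkage.** Let p be true linkage, Se the share of linked users recorded as linked, and Sp the share of unlinked users recorded as unlinked.

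Observed linkage = Se × p + (1 − Sp) × (1 − p). Assume p = 0.70 in both channels.

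*Larger error.* The register misses 15% of linkers; 10% of non-linkers self-report linkage.
- Register: 0.85 × 0.70 = 0.595
- Self-report: 0.70 + 0.10 × 0.30 = 0.730
- Spurious RR = 0.595 / 0.730 = 0.82

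*Milder error.* The register misses 10%; 5% of non-linkers over-report.
- Register: 0.90 × 0.70 = 0.630
- Self-report: 0.70 + 0.05 × 0.30 = 0.715
- Spurious RR = 0.630 / 0.715 = 0.88

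Chance of p<0.05 (two-sided test of two proportions, normal approximation), although true linkage is equal:

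| Reactive users per channel | Larger error | Milder error |
|---|---|---|
| 200 | 82% | 44% |
| 300 | 94% | 60% |

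**Step 4: sensitivity to the assumed errors (p = 0.70).**
- Register Se 0.95, Sp 1.00 against self-report Se 1.00, Sp 0.95: 66.5% against 71.5%, RR 0.665 / 0.715 = 0.93, significant in about 19% of studies at 200 per channel.
- Register Se 0.75, Sp 1.00 against self-report Se 0.95, Sp 0.80: 52.5% against 72.5%, RR 0.525 / 0.725 = 0.72, significant in about 99%.

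**Step 5: selective response alone.** If 50% of linked users respond and r₀ of unlinked users do, observed linkage = 0.70 × 0.50 / (0.70 × 0.50 + 0.30 × r₀).
- r₀ = 0.50: 70.0%
- r₀ = 0.40: 0.35 / 0.47 = 74.5%
- r₀ = 0.25: 0.35 / 0.425 = 82.4%

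Follow-up intensity also differs by modality (5% sample, all consenting clients, registers), so this bias need not be equal across channels.

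**The case against.** The strongest reply is that the sections can be reconciled. Limitations does not rule comparison out. It ranks priorities, promises results by modality and mentions selection and scale-up of models, so a test by modality is consistent with it. The Discussion sentence is a statement of implications, and the same section calls the expected outcomes preliminary. This stands as far as it goes: it would be wrong to read Limitations as a disclaimer of all comparison. The remaining problem is that the Discussion claims more than Limitations allows.

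Other points also stand:

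- A reader might infer that every channel has its own source. Table 1 does not support that, as the grouping above shows.
- A reader might infer that any ranking is a product of measurement. That does not follow. Onsite confirmation and ART initiation are features of service delivery, not outcome sources, and may truly raise linkage. The populations differ too.
- The sentence on risk ratios names no covariates. Only the χ²/Fisher sentence names modality, so modality risk ratios are likely but not stated.
- The article speaks of merging distribution data with users' self-reported data. Whether register checks and reports about partners enter the analysed outcome is therefore unclear, and the register-against-self-report contrast may not arise in that form.
- The error rates in the illustration are assumed and set to push the two channels apart. Errors in the same direction would shrink the spurious difference, and errors could also mask a real one.

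None of this supports the unqualified claim to identify the best channels, or supplies the missing acknowledgement that ascertainment varies by modality.

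**Conclusion.** The point holds in a limited form and should be fixed. The Discussion promises more than Limitations supports. The planned test by modality, applied across all channels, cannot separate channel from method of ascertainment where the two coincide, so differences between source groups are partly confounded with measurement. Comparisons within a group, such as hotspots against transport hubs, are much less affected.

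The size cannot be derived from the documents. With equal true linkage of 70%, the two main error scenarios give a spurious RR of about 0.82 to 0.88, significant in roughly 44% to 82% of studies with 200 reactive users per channel. The wider assumptions span RR 0.72 to 0.93. These figures show that the mechanism could matter. They do not estimate the bias in this study and do not show that a significant result would be spurious.

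**What to change.** - **Discussion:** replace the claim about the best channels with wording such as: *The findings will give preliminary, descriptive results on linkage by distribution channel, to be read with the way linkage was ascertained in each.*
- **Statistical analysis:** report linkage and treatment by modality with 95% CIs, each labelled by outcome source. Base tests of difference on modalities that share a source: first-person self-report by telephone or mHealth; home revisit; report about a partner or network member; register. Treat contrasts across sources as descriptive. Analyse partners and network members reported on by others separately from users reporting their own result.
- **Data collection or Statistical analysis:** state whether register checks and reports about others enter the analysed outcome, and name the source for outpatient departments and GP or nurse-led clinics. Until it is named, their results stay descriptive.
- **Limitations:** add that ascertainment of linkage differs by modality and may account for part of any difference between channels.

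The cost is small: rewording and stratified tables from data already collected. The overall test across all modalities becomes descriptive and the best-channel claim is dropped. Channels can still be described side by side, so the stated aim of evaluating different distribution models is kept.
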